### Sample size

Sample size has been determined to detect a 1.0×10^–3^ (SD 1.3×10^–3^) mm Hg^-1^ improvement in ascending aortic distensibility in the intervention group relative to placebo at 12 months: a difference that we have previously shown to be associated with clinical difference in survival to death or cardiovascular event at 2 years.^21^ To achieve a power of 90% with alpha=0.05 requires 37 patients per group (74 in total). We assume a dropout rate of 20% over 12 months of follow-up (a conservative estimate based on previous studies) and aim to recruit 90 participants in total.

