### Randomisation sequence generation

A computer-generated code list is provided by Sealed Envelope (Sealed Envelope, London, UK) in a password-protected file to drug manufacturer (Tayside Pharmaceuticals) to produce identical, sequentially numbered bottles containing either vitamin K or placebo. The code list is organised in random permuted blocks to facilitate unstratified 1:1 allocation ratio.

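### Ninety recruits at the assumed 20% dropout leave 72 evaluable patients rather than the required 74, a small slip in the dropout inflation with little effect on power

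*Protocol article*

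**What the plan says.** All the figures are in the Sample size section of the protocol article.

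- **Target difference and SD:** "Sample size has been determined to detect a 1.0×10^–3^ (SD 1.3×10^–3^) mm Hg^-1^ improvement in ascending aortic distensibility". The comparison is vitamin K against placebo after one year.
- **Requirement:** "To achieve a power of 90% with alpha=0.05 requires 37 patients per group (74 in total".
- **Dropout and recruitment:** "We assume a dropout rate of 20% over 12 months of follow-up (a conservative estimate based on previous studies) and aim to recruit 90 participants".

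The section on randomisation sequence generation describes "random permuted blocks to facilitate unstratified 1:1 allocation ratio", so equal arms are intended. Follow-up and timetable reports that all 90 participants had been randomised by the end of June 2018. Statistical considerations sets the primary analysis as ANCOVA with baseline distensibility, age and duration of end-stage kidney disease as covariates. The article does not say how 74 was inflated to 90.

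**The concern.** Three figures are printed together and should be linked by simple arithmetic: the number required at analysis, the expected loss and the number recruited. The first two do not lead to the third. A recruitment target inflated for dropout should return at least the required number once the dropout is taken off, and this one falls two short.

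What is at stake is the accuracy of the sample-size justification for the primary endpoint, which a results paper may well repeat. A reader who takes the paragraph at face value will believe that the trial can lose 20% of its participants and still have the 74 it asks for. It cannot, although the shortfall is small.

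**Working it through.** **Inputs (Sample size section).** Difference δ = 1.0 × 10⁻³ mm Hg⁻¹; SD σ = 1.3 × 10⁻³ mm Hg⁻¹; alpha 0.05; power 90%; dropout 20%; 90 recruits; allocation 1:1. The article does not state whether alpha is one- or two-sided. Two-sided is assumed because it reproduces the stated size and one-sided does not.

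**Step 1: reproduce the 37 per group.** The standardised difference is 1.0 / 1.3 = 0.769.

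- Normal approximation, two-sided: n = 2σ²(1.960 + 1.282)² / δ² = 2 × 1.69 × 10.51 ≈ 35.5, so 36 per group.
- The same formula, one-sided: 29 per group.
- Exact t-test, two-sided: n = 36.50, so 37 per group.

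The exact two-sided t-test matches the stated 37, so the requirement of 74 is correct on the stated inputs.

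**Step 2: apply the stated dropout to the stated recruitment.**

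- Evaluable: 90 × (1 − 0.20) = 72, or 36 per group. This is 2 fewer than 74.
- Recruits needed for 74: 74 / (1 − 0.20) = 92.5, so 93.
- With equal arms: 37 / 0.80 = 46.25, so 47 per group, 94 in all.
- Largest dropout that leaves 74 of 90: 1 − 74/90 = 16/90 = 17.8%.

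**Step 3: where 90 may have come from.** Multiplying by 1.2 instead of dividing by 0.8 gives 37 × 1.2 = 44.4, so 45 per group and 90 in all. This fits, but it is a conjecture.

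**Step 4: effect on power (two-sided alpha 0.05, δ/σ = 0.769).**

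| Evaluable per group | Exact t-test | Normal approximation |
|---|---|---|
| 37 | 90.4% | 91.1% |
| 36 | 89.6% | 90.4% |

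The t-test column is the relevant one, because it is the method that reproduces the 37. The loss is 0.8 points from 37 to 36 per group, and 36 per group is 0.4 points below the 90% target.

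**Step 5: how easily the loss is recovered.**

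- With an SD of 1.29 instead of 1.30 (× 10⁻³), the t-test at 36 per group gives 90.0%. The article gives the SD to one decimal.
- Suppose 1.3 × 10⁻³ is the unadjusted SD, and let r be the correlation between baseline and 12-month values. ANCOVA then reduces the SD to σ√(1 − r²). Power at 36 per group is about 92% for r = 0.3, 96% for r = 0.5 and 99% for r = 0.7. An r between 0.12 and 0.13 is enough for 90%, even after three degrees of freedom are spent on covariates. The article gives no value of r and does not say whether the SD is adjusted, so all of these are assumptions.

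**The case against.** The best case for leaving the paragraph alone is that nothing of substance is wrong. The power calculation reproduces. At 72 evaluable patients the power is 89.6%, which rounds to the stated 90%, and the shortfall lies within the rounding of the SD. The normal approximation even gives 90.4% at 36 per group. The authors call the 20% rate conservative, so 72 is their cautious case rather than their expectation. The planned ANCOVA would probably recover more than is lost.

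Most of this stands, and it rules out a stronger reading. A reader might infer that the trial's 90% power claim fails on its own inputs, or that the trial is underpowered. The article does not support that. Its power claim is that 37 per group suffice, which is correct. The abstract says only that the study is powered to detect the target difference and gives no percentage.

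The objection does not remove the mismatch itself. The normal approximation gives a requirement of 36 per group, not the 37 that the article states, so it cannot be used to rescue 36. Calling the 20% conservative does not change the arithmetic: it is the rate the section chose to plan on. The section does not invoke covariate adjustment to justify 90, and the gain depends on a correlation that is not given. Nor is this a matter of an article condensing a longer document, since all three figures are printed and conflict as printed.

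**Conclusion.** The step from 74 evaluable to 90 recruited does not match the stated 20% dropout. Ninety recruits give 72 evaluable patients at that rate, and they keep 74 only up to 17.8% dropout. The shortfall is 2 evaluable patients, or 3 to 4 recruits. The 37-per-group requirement is sound, and the effect on power is minor.

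The recruitment arithmetic needs only the printed figures. The power figures assume a two-sided, unadjusted t-test with the stated difference and SD, and an even split of 36 per group. This is a genuine but minor error. No design, analysis or conclusion depends on it.

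**What to change.** Replace the dropout sentence in the Sample size section with wording such as:

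> 90 randomised; 74 evaluable (37 per group, 90% power) if dropout is no more than 17.8%; at 20% dropout, 72 evaluable (36 per group) give 89.6% power by unadjusted t-test.

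If the results paper repeats the sample-size justification, it should use the same figures. No further recruitment is needed. The cost is one sentence and a planned power that reads slightly less favourably at 20% dropout.

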### Follow-up and timetable

The study timetable is illustrated in figure 1. Recruitment commenced in September 2017 and all 90 participants were recruited and randomised by end June 2018. The study will complete when the last participant completes the last follow-up visit (estimated by July 2019). Results are expected by December 2019.

### Registration

ViKTORIES was prospectively registered with ISRCTN Registry on 26/09/2017 (ISRCTN22012044).

### Safety considerations

Menadiol diphosphate has few undesirable effects but allergic reactions have been known to occur rarely. Haemolytic anaemia has occurred rarely and is more common in G6PD deficiency; we exclude patients with this disorder. Similarly, we exclude patients with allergies to any constituent components of the intervention, including gelatine (found in capsules), lactose and cellulose (used as packing materials with menadiol diphosphate and as placebo). Patients will have monitoring of renal transplant function and immunosuppression levels in addition to standard care. All adverse events are recorded from the time a participant consents to join the study until the last study visit. Participants in this trial are expected to have multiple comorbidities and high levels of illness. The following are therefore classed as expected within this cohort of patients: death or hospitalisation due to new cardiovascular event, new diagnosis or treatment of cancer, fall or fracture, infection, exacerbation of an existing medical condition, deteriorating renal function, high or low potassium levels, nausea, vomiting, constipation or diarrhoea; admission for elective or planned investigation or treatment. For the purposes of this study, only suspected unexpected serious adverse reactions are collected in an expedited manner and reported to the sponsor via the pharmacovigilance office (within 24 hours of the site becoming aware of the event). These events are determined if they are suspected to be caused by the intervention (ie, an unexpected SAE that occurred after the initiation of the intervention and without a clear alternative explanation) but the events are not in keeping with information known about menadiol diphosphate. Participants with unresolved adverse events at the last study visit will be followed up until resolution or 30 days (whichever is sooner).

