### Statistical considerations

The ViKTORIES study has a statistical analysis plan in line with Consolidated Standards of Reporting Trials (CONSORT) guidelines. We will analyse differences between treatment and placebo groups by intention to treat as the primary analysis, and will conduct per-protocol analyses as sensitivity analyses. Analysis of the primary outcome (between-group difference in ascending aortic distensibility at 12 months) will be performed by ANCOVA adjusting for age, duration of ESKD and baseline values. Secondary analyses will similarly be by between-group ANCOVA, adjusting for age, duration of ESKD and baseline values of the variable of interest. All prespecified secondary outcomes will be reported in study publications. Subgroup analyses will be performed in older versus younger participants (age >65 vs <65 years) by analysing for heterogeneity of treatment effect. As a sensitivity analysis, we will perform multiple imputation for missing data for the primary outcome if the assumption of Missing at Random is met. The number and characteristics of serious adverse events (SAE) will be summarised as a whole and by study arm. Analyses will be conducted using R statistical software package (R V.3.5.3 or higher).

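### The article makes absence of a clear alternative explanation a condition for suspecting the drug, which could keep some possibly related serious events off the 24-hour reporting route

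*Protocol article*

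**What the plan says.** All of the operative text is in the protocol article, mostly under Safety considerations.

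- **Scope of rapid reporting:** "only suspected unexpected serious adverse reactions are collected in an expedited manner and reported to the sponsor via the pharmacovigilance office", with a limit of 24 hours from the site learning of the event. No other expedited route is described.
- **Causality:** "These events are determined if they are suspected to be caused by the intervention". A parenthesis opening with *ie* then explains what this means: an unexpected serious event that "occurred after the initiation of the intervention and without a clear alternative explanation".
- **Expectedness against the product:** a further condition follows the parenthesis, namely that "the events are not in keeping with information known about menadiol diphosphate".
- **Expectedness against the cohort:** earlier in the section a broad list of events is introduced with "The following are therefore classed as expected within this cohort of patients". The reason given is that "Participants in this trial are expected to have multiple comorbidities and high levels of illness".
- **Other capture:** the section has every adverse event recorded between consent and the final visit. Statistical considerations adds: "The number and characteristics of serious adverse events (SAE) will be summarised as a whole and by study arm".

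**The concern.** Causality and expectedness are separate judgements. Causality asks whether the drug may have caused or contributed to the event. Expectedness asks whether the event, if caused by the drug, is already known. The parenthesis asks something else: whether the event followed the start of treatment and whether anything else clearly accounts for it. A clear competing cause and a contribution from the drug can both be present in one patient. When they are, the written rule settles the matter against the drug.

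This matters more in a cohort that the article itself describes as heavily comorbid, where competing causes will be found more often than in healthier participants. The stake is speed of notification. An event that fails the causality test does not go to the pharmacovigilance office by the 24-hour route. With 90 participants allocated 1:1, about 45 receive the drug, so an uncommon reaction is more likely to be noticed from an individual case than from a difference in counts between arms at the end.

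**Working it through.** The article states no figure on this point, so the check is a reading of the rule.

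**Step 1: is the parenthesis a definition?** It opens with *ie*, not *eg*, so it says what being suspected means. Its elements are joined by *and*, so each is necessary: the event is an unexpected serious adverse event, it began after the intervention started, and it has no clear alternative explanation.

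**Step 2: apply it.** Take serious events that began after treatment started, are not on the cohort list and do not fit the known product information. They have thus already passed expectedness. Compare the article's rule with a test of reasonable possibility.

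| Alternative explanation | Drug contribution reasonably possible? | Article's rule | Reasonable-possibility rule |
|---|---|---|---|
| None | Yes | Expedited | Expedited |
| Possible, but not clear | Yes | Expedited | Expedited |
| Clear | Yes | **Not expedited** | **Expedited** |
| Clear | No | Not expedited | Not expedited |

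The rules part in the third row only. That row is the whole of the concern, and it is excluded by the causality clause alone, since expectedness has already been passed.

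**Step 3: the merging of the two tests.** The word *unexpected* stands inside the explanation of causality, and a product-based expectedness condition is then added after it. Read literally, an expected serious event cannot be classed as suspected at all, so a related but expected event has no category of its own. Causality and expectedness cannot then be read off as two separate answers.

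**Step 4: where the effect stops.** Recording of adverse events carries no causality filter, nor does the by-arm summary of serious events. A third-row event stays in the data and in the final comparison. What it loses is notification within 24 hours.

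**Step 5: can a size be given?** The number of third-row events depends on the rate of unexpected serious reactions to the drug and on the share of them with a clear alternative cause. The documents give neither, so no estimate is made.

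**The case against.** **The bar is a clear alternative, not any alternative.** This stands. A reader might infer that nearly every serious event in this cohort would be dismissed, or that real reactions would be screened out. The text does not support that. An event with only a possible or competing comorbid cause still qualifies (second row of the table). The supportable word is *could*.

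**The loss cannot be quantified.** This also stands. A reader might try: with 45 on the drug and an assumed reaction rate of 2%, the chance of at least one case is 1 − 0.98^45 = 60%. If half of such cases had a clear alternative cause, the chance that one passes is 1 − 0.99^45 = 36%; if nine in ten did, it is 1 − 0.998^45 = 9%. The arithmetic is right, but the inputs have no basis in the documents and the fall is driven by the assumed share. It also ignores expectedness. The cohort list already removes many of the events for which a comorbid cause is most readily found, and the causality clause acts only on what remains.

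**Expedited reports are not the only safety information.** This stands too. All adverse events are recorded, transplant function and immunosuppression levels are monitored beyond standard care, and Ethics describes sponsor monitoring, an audit in 2018 and annual reports to the ethics committee and the funder. It would be wrong to call the 24-hour route the only early signal. It is the only expedited route described.

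**The operative wording may lie elsewhere.** Ethics says that the sponsor's procedures apply, and the full protocol is not shown. That limits what can be said about how assessors classify events in practice. It does not cure the rule that the article states: if the other documents differ, the article misreports them; if they agree, the rule itself needs correcting.

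**The change comes late.** Follow-up and timetable has all 90 participants randomised by the end of June 2018, with follow-up ending about July 2019. This raises the cost, because events already classified need checking, but it does not make the wording sound.

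**Conclusion.** The point holds in a limited form. As written, absence of a clear alternative explanation is a necessary condition for an event to be suspected, and expectedness is mixed into that test. In a cohort described as highly comorbid, this could keep some possibly drug-related, unexpected serious events off the 24-hour route. Those events would still be recorded and counted by arm, so neither the data nor the final safety comparison is affected. The number involved cannot be estimated from the documents, and nothing in them shows that any reaction has been or will be missed. The conclusion rests on reading *ie* as introducing a definition and on the article reflecting the rule in use.

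**What to change.** Replace the parenthesis under Safety considerations with a causality test on its own: an event is suspected when there is a reasonable possibility that the intervention caused or contributed to it, judged without knowledge of allocation. Record expectedness as a separate judgement. Note any alternative explanation on the serious adverse event form as information, not as an automatic exclusion. Reconcile the wording with the full protocol and the sponsor's procedures, so that all three state the same test.

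The cost is a short amendment to the text and to the form guidance, a few extra expedited reports, and a blinded check of serious adverse events already classified. No dose, treatment rule or efficacy analysis changes.

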### Dissemination plan

Complete trial data will be submitted for presentation at an international meeting and will be published in a peer-reviewed journal, and shared on social media. After publication, ViKTORIES participants will be informed of trials results by letter and the dataset will be contributed to the Virtual International Renal and Transplant Trials Archive (www.virtualtrialsarchives.org/virtta).
